**METHODS**

**Study setting**

The study will be carried out at the Obstetrics and gynecology clinics of Nnamdi Azikiwe University Teaching Hospital (NAUTH), Nnewi, a tertiary hospital in the South-east Nigeria, as well as other collaborating hospitals in south-east Nigeria.

**Study design**

This will be an open-label randomized clinical trial.

**Study population**

The participants will comprise both obstetrics and puerperal adult patients with clinical and laboratory diagnosis of anemia and who will be give written informed consent before recruitment. The patients will be recruited at the outpatient clinic or antenatal clinics or referred for treatment of their anemia, in the hospital.

**Inclusion criteria**

Both obstetrics and puerperal adult patients with confirmed clinical and laboratory diagnosis of anemia (<10.0 g/dl) and with normal liver and renal function markers or profiles will be included.

**Exclusion criteria**

- Pregnant women at first trimester of pregnancy (because of nausea and vomiting at this period).
- Multiple gestation
- Chronic medical disorders including HIV/AIDS, Cancers, etc.
- Women on chronic medications that cause anemia

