In one recent report, anemic pregnant women of gestational age of 36 weeks with IDA of hemoglobin level of 5g/dl received Mojeaga in addition with oral iron therapy (adjunct therapy) for two weeks, and had their hemoglobin appreciated to 10 g/dl two weeks after treatment without any adverse pregnancy outcome or neonatal outcome [8]. In other published reports, significantly higher number of women achieved anemia correction within a shorter time frame, and there were markedly fewer gastrointestinal treatment-related adverse events especially when the drug is administered in sips [9, 10, 11]. This lends support to the hypothesis that Mojeaga in combination with oral iron therapy is superior to oral iron therapy alone for correcting anemia in gynecological and obstetrics patients.

To our knowledge, this is the first randomized study that will be reporting on efficacy and safety of combined Mojeaga and oral iron therapy schedule. Therefore, this proposed study is aimed at determining the effectiveness, safety and tolerability of Mojeaga as adjunct to conventional oral iron therapy for correcting anemia in gynecological and obstetrics patients.

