**OUTCOME MEASURES**

**PRIMARY**

1. Mean or median hematocrit level at two weeks after initial therapy.
2. Changes in the hematocrit level at two weeks after initial therapy.

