**Follow-Up**

The trial is expected to last for at least 16 months. Recruitment will be within the first 6 months of commencement of the study and the follow up will be for at least 10 months from recruitment (ie total of 16 (6+10) months). All participants will be followed up in outpatient settings. During each follow-up weekly visit, patients will be contacted on phone on weekly basis to assess level of compliance. The patients will also be encouraged to record any side effects or adverse events in a paper that will be reviewed at each follow-up visit, and they will be explicitly asked about such events during each interview. The drug compliance will be checked before follow-up test. Any patient found to be developing complications such as worsening of the

symptoms from the study will be given appropriate treatment. Repeat hemoglobin level will be done 2 weeks post initiation of treatment in all the participants to confirm success of treatment (correction of anemia and levels of hemoglobin/hematocrit levels) and absence of adverse effects. All the pre and post (repeat) hemoglobin/hematocrit level will be carried out by hematologist: [name], while the LFT, Lipid profiles and SEUCR will be carried out by the Senior laboratory Scientist of Chemical Pathology- [name] in Nnamdi Azikiwe University Teaching Hospital, Nnewi laboratory.

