**FETAL/NEONATAL OUTCOME during therapy**

1. **Preterm labour** a.) YES----b.) NO------
2. **Preterm PROM** a.) YES----b.) NO------
3. **Birth weight (kg)----------------------------**
4. **Birth anomaly---------------**

**PROFORMA: Efficacy and safety of Mojeaga® in combination with conventional oral iron therapy for correcting anemia in gynecological and obstetrics patients: a pilot randomized clinical trial in NAUTH, Nnewi.**

**NAME OF DOCTOR................................................CODE NUMBER OF PATIENT………………………**

(1). COMPUTER NUMBER OF PATIENT..........................(2) GENDER…………………………

(3). DATE OF RECRUITMENT......................(4) TIME..................(5) AGE.......................

(6.) Marital status: Married [ ] [single [ ] Divorced [ ](7.) LMP………..(8)GESTATIONAL AGE..............

(9). Parity.................(10). Body weight-.............(11). Height: (cm)......................................................

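### With no upper gestational-age limit, some women may deliver before the week-2 hematocrit, and the form records no delivery date to identify them

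*Combined protocol and SAP*

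**What the plan says.** Under Inclusion criteria the trial takes "Both obstetrics and puerperal adult patients with confirmed clinical and laboratory diagnosis of anemia (<10.0 g/dl") whose liver and renal markers are normal. The Exclusion criteria contain one limit on gestational age: "Pregnant women at first trimester of pregnancy (because of nausea and vomiting at this period"). Neither section has an upper limit or a criterion based on expected delivery.

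The two primary outcomes are "Mean or median hematocrit level at two weeks after initial therapy" and "Changes in the hematocrit level at two weeks after initial therapy". Follow-Up fixes the timing for everyone: "Repeat hemoglobin level will be done 2 weeks post initiation of treatment in all the participants". No exception is made for a delivery in between.

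Statistical Analysis compares means with an independent t-test. It names no covariate and no sensitivity analysis, and offers subgroup analysis only where possible. Randomization and Allocation Sequence mentions no stratification.

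The proforma records last menstrual period and gestational age at recruitment. Its section "FETAL/NEONATAL OUTCOME during therapy" has fields for preterm labour, preterm rupture of membranes, birth weight and birth anomaly. It has no field for delivery date, blood loss or transfusion.

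**The concern.** A woman randomised close to term is eligible and may be pregnant at baseline but puerperal at the outcome. Her change in hematocrit then reflects blood lost at delivery, the postpartum fluid shift and any transfusion, as well as two weeks of treatment. The plan has no rule for this event in eligibility, stratification, the model or a sensitivity analysis. A completed birth-weight field would hint that a birth occurred. Without a date, however, the analyst cannot tell whether it came before or after the blood sample.

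At stake is what the primary comparison means. The plan asks whether adding Mojeaga raises hematocrit. In women who deliver in the window, a large part of the measured change may have nothing to do with either treatment. That adds variance, and a chance difference between arms in the number of deliveries would move the estimate.

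**Working it through.** **Inputs from Sample size determination.** Week-2 means 29.1% and 31.5% (difference 2.4), SD 2.5; change from baseline 6.5 and 10.5 (difference 4.0), SD 3.8; 80% power; 15% dropout; 47 per arm. Statistical Analysis sets significance at 0.05, taken here as two-sided.

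**The plan's own figure.** n per arm = 2 × (1.96 + 0.84)² × 2.5² / 2.4² = 17.03, rounded up to 18. With dropout, 18 / 0.85 = 21.2, rounded up to 22, or 44 in total against the stated 94. Power for the 4.0-point change is 99.9% at 47 per arm and 99.6% at 39, against the stated 97%. The mismatch is a separate matter. Here it means only that, on the stated SD, the trial has power to spare.

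**How many women could be affected.** The documents do not say. Assume entry is spread evenly over gestation. From 14 to 40 weeks, 2/26 = 7.7% of pregnant entrants are in the last two weeks; from 28 to 40 weeks, 2/12 = 16.7%. These are shares of pregnant women only, because puerperal participants cannot contribute. If half the participants are puerperal (assumption), the shares of all participants are 3.8% and 8.3%. Reaching 15% of all participants would need 0.15 / 0.167 = 90% pregnant, entry only from 28 weeks, and every woman in the last two weeks delivering before her test. So 15% is a high case.

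**Effect on variance and power.** Let p be the share of all participants who deliver before the test, and let d and s be the mean and SD of the delivery-related fall, additive and equal in both arms. Added variance = p(1 − p)d² + p·s². Power = Φ(Δ / (SD × √(2/39)) − 1.96), where 39 is 47 × 0.85 rounded down. The values of p, d and s are assumptions.

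| p | d, s | Added variance | SD, week 2 | Power, Δ = 2.4 | SD, change | Power, Δ = 4.0 |
|---|---|---|---|---|---|---|
| 0 | – | 0 | 2.50 | 98.9% | 3.80 | 99.6% |
| 5% | 2, 2 | 0.39 | 2.58 | 98.4% | 3.85 | 99.6% |
| 5% | 4, 3 | 1.21 | 2.73 | 97.3% | 3.96 | 99.4% |
| 10% | 2, 2 | 0.76 | 2.65 | 97.9% | 3.90 | 99.5% |
| 10% | 4, 3 | 2.34 | 2.93 | 95.1% | 4.10 | 99.1% |
| 15% | 2, 2 | 1.11 | 2.71 | 97.4% | 3.94 | 99.4% |
| 15% | 4, 3 | 3.39 | 3.10 | 92.7% | 4.22 | 98.7% |

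The variance of the week-2 value thus rises by 6% (0.39/6.25) to 54% (3.39/6.25). An exact t calculation gives power less than one percentage point lower in each row.

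**Chance imbalance.** At p = 10% and 47 per arm, the standard error of the difference in delivery share is √(2 × 0.10 × 0.90 / 47) = 6.2 percentage points. A 10-point imbalance, about 1.6 standard errors, would shift the arm difference by 0.10 × 2 = 0.2 to 0.10 × 4 = 0.4 points, against a target of 2.4. This is part of the added noise in the table, not a further loss.

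**The case against.** The strongest reply is that the plan asks for week-2 hematocrit by arm in a mixed obstetric and puerperal population. Under randomisation, a comparison that includes women who deliver is valid for that population, and power holds in every row above. This stands. It limits the point to precision and interpretation.

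Three stronger readings are tempting, and the documents do not support them.

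- A reader might infer that near-term women will be enrolled in number and will be tested after delivery. The criteria only permit this, and being due within two weeks does not mean delivering before the test. The Introduction supports the use of Mojeaga with a report of "anemic pregnant women of gestational age of 36 weeks with IDA of hemoglobin level of 5g/dl received Mojeaga". Two weeks on, such women are at about 38 weeks, so the report shows late-pregnancy use, not delivery in the window. The form's heading does refer to the therapy period. But Follow-Up also plans at least 10 months of observation, so a birth-weight field does not prove that births within two weeks are expected.
- A reader might infer bias towards one arm. Treating staff are not blinded, and nothing guards against different peripartum management by arm. But nothing in the documents shows that it would differ.
- A reader might infer that recently delivered women will miss the visit. No attendance figure supports this, and the plan has weekly phone contact and allows for 15% dropout.

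**Conclusion.** The point holds in a limited form. Eligibility lets women due within two weeks enter. Both primary outcomes are measured once, at week 2, and neither the analysis nor the form can isolate a delivery in between. Expected bias is zero. The cost is a noisier endpoint that is harder to interpret.

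The size is unknown. With 5–15% of all participants delivering in the window and a fall of 2–4 points, power for the 2.4-point difference stays above about 90%. This rests on the stated SD of 2.5, on 39 evaluable women per arm, and on a fall that is additive and equal in both arms. Power drops below 80% only in an extreme case: 30% delivering with a 6-point fall (SD 3) gives 74%. That share is well above the 16.7% found for pregnant women entering only from 28 weeks. The case for change is therefore a clearer endpoint at low cost, not rescue of an underpowered trial.

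**What to change.** - **Eligibility.** Add to the Exclusion criteria pregnant women whose expected or scheduled delivery falls before the week-2 test. The investigators should set the cutoff. Allow one re-screening after delivery as a puerperal participant, a group already eligible. If near-term women are wanted in the trial, say so and keep the remaining steps.
- **Form.** Add delivery date and any transfusion. These remain useful after the exclusion, since unexpected early deliveries will still occur.
- **Primary analysis.** Keep the week-2 sample as the primary value for every randomised woman, whether or not she has delivered. Replace the unadjusted t-test with a linear model that includes pregnant or puerperal status at entry. Do not substitute a sample taken on admission in labour: it would reflect shorter treatment and be timed by an event after randomisation.
- **Sensitivity analysis.** Repeat the comparison without women who delivered before the test, and state that this conditions on a post-randomisation event. Report the number of such women by arm.

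The cost is a protocol amendment, two form fields and one extra analysis. A few near-term women are deferred, which may slow recruitment slightly, and the population becomes slightly narrower.

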**Randomization and Allocation Sequence**

Following consent, patients at the selected hospitals will be screened for eligibility. The patients, eligible for the study, will be randomized into two groups using simple (block) randomisation using a radomisation table to be created by a computer software program by a person not involved in the study and available at [**http://mahmoodsaghaei.tripod.com/Softwares/randalloc.html**](http://mahmoodsaghaei.tripod.com/Softwares/randalloc.html). Allocation sequences and codes will be concealed from the person allocating the participants to the intervention arms using numbered containers containing the drugs.

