**Blinding of participants, Personnel and Outcome assessors**

Only the outcome assessors will be blinded (open-label trial).

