**Study Procedure/Drug Administration**

Patients with a clinical and laboratory diagnosis of anemia presenting in Outpatient Clinic or antenatal clinic of NAUTH Nnewi for symptoms or signs of anemia will be screened consecutively. All patients will also undergo routine medical examination including pulse rate, body weight, blood pressure determination and general examination to ascertain the presence of and severity of anemia. All consenting patients will be diagnosed to have either anemia or not after undergoing hematological test. Only patients with confirmed clinical and laboratory diagnosis of anemia will be randomized. Eligible patients will be sequentially allocated using an opaque sealed envelope to receive either Mojeaga and conventional oral Therapy, or the conventional oral iron Therapy alone. Therapies will be giving for two weeks**.**

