**Intervention Therapy**

## Standard doses of 50 mls of Mojeaga will be administered three time daily in conjunction with iron therapy Astyfer (Til Healthcare PVT Ltd, Andhra Pradesh, 517588 India) capsules two times a day (breakfast and dinner) for 2 weeks.

**Control Therapy**

Standard doses of one capsule of Astyfer will be administered alone two times a day (breakfast and dinner) for 2 weeks. These patients with confirmed diagnosis of anemia will be on conventional iron therapy administered without Mojeaga.

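### Allocation concealment rests on two unlinked devices, one of which (numbered drug containers) would probably reveal the next arm; the sequence is also called both simple and block

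*Combined protocol and SAP*

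**What the plan says.** Two sections of the combined protocol and SAP describe how the next assignment is hidden.

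- Randomization and Allocation Sequence: the sequence and codes are "concealed from the person allocating the participants to the intervention arms using numbered containers containing the drugs". The same section says that patients are "randomized into two groups using simple (block) randomisation", from a computer-made list prepared by someone outside the study. It gives no block size. It places consent first, then eligibility screening, then randomisation.
- Study Procedure/Drug Administration: "Eligible patients will be sequentially allocated using an opaque sealed envelope". Containers are not mentioned here, just as envelopes are not mentioned in the other section.

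The treatments look different. The intervention section states that "50 mls of Mojeaga will be administered three time daily in conjunction with iron therapy", and the control section states: "Standard doses of one capsule of Astyfer will be administered alone two times a day (breakfast and dinner) for 2 weeks". The control arm has no dummy liquid. The blinding section limits blinding to the outcome assessors.

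**The concern.** In an open-label trial the main protection against selective enrolment is that nobody deciding on a woman's entry knows which arm comes next. If the operative device is a drug container, and one arm's container holds a large volume of liquid while the other's holds capsules only, that protection is doubtful. A fixed block pattern can weaken it further, because staff see each treatment as it is given.

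Foreknowledge could influence who is enrolled, and when. The trial takes both pregnant and puerperal women, sets no lower hemoglobin limit, and has an open-ended exclusion for chronic disorders, so there is room for judgement. The first primary outcome is the hematocrit level at two weeks, and the Statistical Analysis section compares means by an independent t-test with no baseline adjustment. A baseline difference created at entry would carry into that comparison. Adjusting for baseline hematocrit would help with measured severity but not with selection on features that nobody recorded. Blinded laboratory assessment does not address this bias, because it arises before treatment starts.

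**Working it through.** The plan gives no figure for concealment, so there is none to reproduce. The check compares the two descriptions and then sizes the two routes by which the next arm could become known.

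**1. The two devices.** One section names numbered drug containers, the other an opaque sealed envelope. No sentence makes the envelope point to a container or gives either device precedence. Staff at the teaching hospital or at the collaborating hospitals named under Study setting could follow either text and be within the protocol.

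**2. What a container would hold.** Inputs: 50 mL three times daily (Intervention Therapy); two weeks, that is 14 days ("Therapies will be giving for two weeks"); one capsule twice daily (Control Therapy, and the abstract's Methods for both arms).

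- Liquid, intervention arm: 50 × 3 × 14 = 2,100 mL = 2.1 litres.
- Liquid, control arm: 0 mL.
- Capsules: 2 × 14 = 28 in each arm.
- If drug were supplied weekly (an assumption; the plan does not say), the difference would be 50 × 3 × 7 = 1,050 mL per container.

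On either supply schedule the arms differ by a litre or more of liquid. The plan does not describe the containers as opaque, sealed, identical or matched for size and weight.

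**3. What blocks would reveal.** Under simple randomisation, past assignments say nothing about the next one, and the best guess is right 50% of the time. Under fixed blocks with 1:1 allocation, once one arm's quota in a block is used up, the remaining assignments are certain. For a block of 4:

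- The fourth assignment is always certain: probability 1.
- The third is certain when the first two match: 2 of the 6 possible orders, probability 1/3.
- Share certain = (1 + 1/3) / 4 = 1/3.

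The plan gives no block size, so the range over assumed sizes is:

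| Assumed fixed block size | Assignments known with certainty | Best guess correct |
| --- | --- | --- |
| 2 | 50% | 75% |
| 4 | 33% | 71% |
| 6 | 25% | 68% |
| 8 | 20% | 67% |

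These figures assume a recruiter who knows the block size and has seen every earlier assignment on the list.

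**The case against.** Much of a sound procedure is already in the text. A person outside the study makes the list, consent and screening precede randomisation, only women with confirmed anemia are randomised, and the envelopes are opaque, sealed and used in sequence. All of that stands. It protects the making of the list and, if the envelope text governs, most of the next assignment too. Numbering of the envelopes and the conditions for opening them are still missing, and the container text still competes with the envelope text.

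A reader might infer three stronger things that the documents do not support.

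- *That the two descriptions are incompatible.* An envelope could hold the number of a container that is issued after assignment. The plan does not say so, but it does not exclude it. What is shown is that the two sections are not reconciled.
- *That containers cannot conceal, or that the next arm is predictable every time.* The plan does not say that recruiters handle containers before enrolment, that packs are see-through or unmatched, or that each holds the full two-week supply. Opaque outer packs matched for size and weight could work. If only envelopes are used, the volume argument falls away.
- *That simple randomisation would leave damagingly unequal arms.* A split of 42 v 52 has an effective size of 2 × 42 × 52 / 94 = 46.5 per arm against 47, a loss of about 1%. Chance imbalance in numbers is therefore not part of this point. Nor could it occur together with the block figures, since they belong to different readings of the same phrase.

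The block figures have limits of their own. With one list shared across hospitals, a recruiter at one site would not see every earlier assignment. The wording could also mean unstratified blocks, which would fit the planned 47 per arm, but the plan leaves the reader to guess.

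Open-label treatment is a legitimate choice and is not criticised here; allocation can be concealed without blinding treatment.

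**Conclusion.** The point holds as a conflict between two stated rules, one of which carries a real risk of selection bias. If the container rule is followed as written, a difference of about 2.1 litres of liquid would probably reveal the next arm to anyone who handles the containers before enrolment. That rests on two assumptions which the plan neither confirms nor rules out: that containers are the operative device, and that recruiting staff have access to them. If fixed blocks are used and both their size and the earlier assignments are known, between 20% and 50% of assignments could be deduced for blocks of 8 down to 2, and one third for a block of 4. The resulting bias in the hematocrit comparison cannot be sized from the documents. It should be settled before women are randomised, because lost concealment cannot be restored afterwards and the correction is mostly a matter of wording.

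**What to change.** 1. Delete the container wording from Randomization and Allocation Sequence, so that one device governs.
2. In both sections, specify sequentially numbered opaque sealed envelopes. Each is opened only after eligibility and consent are recorded and the participant's code is written on the envelope. Drug is issued after that.
3. Replace the simple-and-block label with permuted blocks of randomly varying size. Keep the sizes with the person who makes the list and do not disclose them to recruiters.

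Separate lists by pregnancy status and hospital are not needed to mend this. With 94 women and an unstated number of hospitals, they could leave many incomplete blocks and let each site see the whole of its own list.

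The cost is a change of protocol wording, a new list and slightly more envelope handling. The plan does not say whether the named software can vary block sizes, so that should be checked before the list is made.
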